### Recruitment

Recruitment began in January 2020 and ended in August 2021.^3^ The first recruitment wave took place in January to February 2020, the second recruitment wave took place between May and October 2020, and the third recruitment wave took place between July and August 2021. Participants were recruited to the study using several methods. A part of the sample was recruited from the BASIC project—a large epidemiology study investigating maternal health during and after pregnancy [56]. Mothers participating in the BASIC-project was asked if they were interested in being contacted by the Uppsala Child and Baby Lab about a study on child development. Recruitment also took place by contacting families with a general interest in participating in child developmental studies at the Uppsala Child and Baby Lab. Other means of recruiting potential participants included sending letters describing the study to families in Uppsala municipality, using advertisement for the study on Facebook, and by putting up flyers and verbally informing parents visiting “open pre-schools” in Uppsala. All potential participants, i.e., caregivers with a child of appropriate age who expressed interest in participating in the study, were provided with an invitational package that described the study and included copies of the consent form. Caregivers who expressed an interest in the study were then screened via telephone for eligibility.

Of 187 dyads assessed for eligibility, 151 met all inclusion criteria and none of the exclusion criteria and gave consent to participate in the study. They were then randomized to an index group or active control group. Of these, 115 completed the baseline assessment, 109 completed the post-assessment, and 98 completed the first follow-up assessment at 18 months. The follow-up assessment at 24 months is still ongoing at the current date.

### Assignment of interventions: allocation

#### Sequence generation

A computer-generated randomization sequence (http://www.randomization.com) was used to allocate participants in a 1:1 ratio to the intervention group and the active control group. Blocked randomization with a 1:1 ratio was used to ensure that the study groups were of approximately the same size.

#### Concealment mechanism

Allocation concealment was released to the participants after being recruited into the study and giving consent to being part of the study prior to baseline assessment. The allocation of participants to the intervention group or the active control group was done by a person on the research team who was not involved in participant assessments.

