#### Blinding (masking)

Due to the nature of the intervention and for ethical reasons, the intervention facilitator and the participants are not blinded to group allocations. They are aware of the existence of two groups (i.e., a reading group and a play group), but not of the study hypothesis. All assessments of participating caregivers and children are conducted by a data collector, who is blind to group belongings. Participating parents are asked to not reveal their group belonging to the data collector. All coders of video data will be blinded to group allocation. Allocation assignment will be concealed to the researchers at the analysis stage.

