### Statistical methods

All statistical analysis will be conducted using the SPSS and R software. Data will be screened to check for data entry errors and to test if the data meet the assumptions of parametric procedures. The pattern and amount of missing data will be examined and handled by using maximum-likelihood estimates (or similar estimates), if appropriate. Baseline data and demographic characteristics will be described using summary statistics (means and standard deviations or number and percentages). Group baseline differences will be assessed using independent samples *t* test, chi-squared test, and Mann-Whitney *U* test. Fidelity in terms of adherence and the dose of the intervention will be summarized using descriptive statistics. All tests will be two-sided and 5% will be used as the level of significance. Effect size measures (e.g., Cohen’s *d*) will be calculated to describe intervention effects.

The statistical analyses of the primary outcomes will be performed blinded to treatment allocation. In accordance with CONSORT guidelines, intention-to-treat principles will be used to prevent systematic bias. Linear mixed models or analysis of covariance will be used to assess intervention effects at post intervention and at the follow-ups. Baseline scores will we controlled for as covariates. Other potential covariates (e.g., child monolingual status) will be investigated by examining correlations between covariates and the outcome variables.

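### Families appear to have learned their arm before baseline, so parent-dependent T1 scores are post-allocation values and need a sensitivity analysis

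*Protocol article*

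**What the plan says.** Three sections of the protocol article give the order of events.

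- Concealment mechanism: allocation was "released to the participants after being recruited into the study and giving consent to being part of the study prior to baseline assessment".
- Recruitment: after 151 dyads had consented, "They were then randomized to an index group or active control group". It continues: "Of these, 115 completed the baseline assessment, 109 completed the post-assessment, and 98 completed the first follow-up assessment at 18 months".
- Blinding (masking): "the intervention facilitator and the participants are not blinded to group allocations". On what parents knew: "They are aware of the existence of two groups (i.e., a reading group and a play group), but not of the study hypothesis". Parents are asked to keep their arm from the data collector, with no exception for baseline. Data collectors and video coders are blind.

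Table 2 lists at T1 the parent-reported CDI (a primary outcome and the only expressive-language measure), EEFQ and reading habits, and the observed parental behaviour in the BSSI and problem-solving tasks. Under Procedure, the caregiver completes the questionnaire online. In the N400/pupil task the caregiver speaks the test sentence to the child (Primary outcome measures).

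Statistical methods plans tests of group differences at baseline and says of the models: "Baseline scores will we controlled for as covariates". Hypothesis and Mediator analysis rely on gains in language and joint attention and on improvements in parental behaviour. Potential moderators includes reading habits, indexed at all four assessments.

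**The concern.** A baseline covariate can be adjusted for safely when allocation cannot have influenced it. That is normally secured by measuring it before randomisation, or at least before the participant learns the result. Here the person who supplies several T1 scores seems to have known the arm. A parent told to expect a reading group might report more words, report more reading, or handle a book differently in the recorded session. A parent told to expect a play group has no such cue.

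Three uses of T1 are then affected. A model that conditions on T1 may remove or add part of the between-arm contrast. A change from T1 may include the shift itself. A test of baseline difference on these measures cannot separate chance imbalance from an effect of knowing the arm. The point concerns the meaning of T1 scores in the 115 dyads who have them, not the dyads lost before baseline.

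**Working it through.** **Order of events.** Recruitment gives 151 randomised, of whom 115 completed baseline: 151 − 115 = 36 dyads, or 36/151 = 23.8%, left between the two. So baseline followed randomisation. That parents had also been told by then rests on Concealment mechanism.

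**The plan's own figure.** Sample size states 55 per arm for d = 0.54, 80% power and two-sided alpha 0.05. The two-sample t solution is 54.8, rounded up to 55, so it reproduces. At the final 59 and 56, power without any covariate is 0.819.

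**Bias formulas.** Work in SD units. Let s be the shift in the index arm's T1 mean caused by knowing the arm, b the T1–T2 slope, and k the fraction of s still present in the T2 report. Then:

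- bias of the T1-adjusted effect = ks − bs = s(k − b)
- bias of the effect without T1 = ks
- bias of the gain score (T2 − T1) = ks − s = −s(1 − k)

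The document gives none of s, b or k. With the assumed values s = 0.2 and b = 0.6:

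| Case | T1-adjusted | Without T1 | Gain score |
|---|---|---|---|
| Only T1 moves (k = 0) | −0.6 × 0.2 = −0.12 | 0 | −0.20 |
| Shift persists in full (k = 1) | 0.2 × (1 − 0.6) = +0.08 | +0.20 | 0 |

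A minus sign means the intervention effect is understated when the index arm's T1 is raised. If T1 is lowered, every sign reverses.

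**Range.** For s from 0.1 to 0.3 and b from 0.5 to 0.8, the size of the bias in the T1-adjusted effect is:

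- k = 0: from 0.5 × 0.1 = 0.05 to 0.8 × 0.3 = 0.24
- k = 1: from 0.1 × 0.2 = 0.02 to 0.3 × 0.5 = 0.15

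The effect without T1 has bias 0 in the first case and 0.1 to 0.3 in the second. The gain score has the reverse.

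**Which model is safer.** The model without T1 has the smaller bias only when k < b/2, that is k < 0.3 at b = 0.6. Otherwise the T1-adjusted model is at least as good, and at k = b it has no bias.

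**Effect on tests, k = 0 only.** With 59 and 56 dyads, correlation 0.5 (equal to the slope when SDs are equal) and s = 0.2:

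- T1-adjusted: bias 0.10; SE = √(0.75 × (1/59 + 1/56)) = 0.162; type I error 0.095; power for d = 0.54 falls from 0.917 to 0.777 if the index arm's T1 is raised.
- Gain score: bias 0.20; SE = √(2 × 0.5 × (1/59 + 1/56)) = 0.187; type I error 0.19; power falls from 0.825 to 0.445.

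**Precision lost without T1.** If the T1–T2 correlation is 0.6, the SE ratio is 1/√(1 − 0.36) = 1.25.

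**The case against.** The strongest reply is that the safeguards are better than the concern suggests. Parents were not told the hypothesis, coders are blind, and under Study design baseline precedes the first session, so no technique had been taught. This stands as a reason to expect a smaller shift. It does not remove one: blind assessors and coders protect neither a parent's own report nor a parent's own behaviour, and the two group names are themselves a cue.

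A second reply is that the final phrase of the Concealment mechanism sentence could attach to the giving of consent, leaving open when parents were told. Recruitment settles when randomisation took place, not when it was disclosed. This stands as a reason to ask for one clarifying sentence. The plain reading is still disclosure before T1.

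A third reply is that dropping T1 could make matters worse, because the same unblinded parent reports the CDI and EEFQ at T2. The persistent case above bears this out. It rules out treating the model without T1 as the correct one.

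A reader might also infer that reading habits enter the moderator analysis as a baseline value only. Potential moderators indexes them at all four assessments and does not say that. Nor does the article define improvement in parental behaviour as a simple T2 − T1 difference, so the gain-score results apply only if that form is used.

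**Conclusion.** The point holds as a limit on interpretation. On the plain reading, T1 scores on the CDI, EEFQ, reading habits, BSSI and problem-solving task are post-allocation values that knowing the arm could have moved. The N400/pupil task may be exposed too, since the caregiver speaks the stimulus. Preferential looking and the ESCS tasks, child measures run by blind staff, are little exposed, and parental education hardly at all.

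A reader might infer that these baselines are in fact biased, or that a known share of the planned effect is lost. The 0.05 to 0.24 SD range would be 9% to 44% of d = 0.54. The document supports neither inference. It shows that a shift was possible, gives no size or direction, and leaves open whether a shift would persist to T2, which changes both the sign of the bias and which model it hurts most. With no shift there is no bias. The figures show how the result depends on assumptions and are not estimates for this trial.

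**What to change.** 1. State when parents learned their arm relative to the T1 questionnaire and the T1 visit. If it was after both, correct Concealment mechanism, and the rest falls away.
2. Keep the T1-adjusted model as primary. For the parent-dependent outcomes (CDI, EEFQ, BSSI, problem-solving), add a reported sensitivity analysis that replaces T1 with covariates that knowing the arm cannot move: child age, child sex and parental education. Say whether N400 and pupil dilation are included.
3. Interpret disagreement between the two models with caution. Do not require both to agree: at d = 0.54, 59 and 56 dyads and a correlation of 0.6, that rule would cut power from about 0.95 to about 0.81.
4. Report the T1 between-arm difference on these measures with its confidence interval, and do not read it as a check on randomisation.
5. Do not rest conclusions on gain scores of these measures alone.

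The cost is one extra model per parent-dependent outcome and a few sentences. The downside is that the model without T1 is less precise (SE about 25% larger at a correlation of 0.6). Releasing allocation only after baseline is relevant to re-use of the protocol, since Trial status reports that recruitment ended in August 2021.

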#### Blinding (masking)

Due to the nature of the intervention and for ethical reasons, the intervention facilitator and the participants are not blinded to group allocations. They are aware of the existence of two groups (i.e., a reading group and a play group), but not of the study hypothesis. All assessments of participating caregivers and children are conducted by a data collector, who is blind to group belongings. Participating parents are asked to not reveal their group belonging to the data collector. All coders of video data will be blinded to group allocation. Allocation assignment will be concealed to the researchers at the analysis stage.

### Data collection

#### Data collector training

A team of data collectors have been trained in lab assessments and administration of the questionnaires. All data collectors had a BA or higher degree in psychology (or equivalent subject) and were trained in the assessments prior to data collection (e.g., by running pilot assessments), including consent and referral procedures. The training and administration of tasks followed a data collector manual developed by LF and JG. To monitor and ensure the fidelity of assessment administration, LF and JG made regular in vivo checks with data collectors and through examination of video records.

### Coding and reliability

Videos of caregiver-child interactions and child joint attention and EF tasks are being coded by independent trained coders who are unaware of participant’s intervention allocation. Reliability will be established from randomly selected 20% of video records per task.

#### Procedure

Data collection occurs at four time points: at baseline, following the 5-week intervention, and 6 and 12-months post intervention. At each time point, the participating caregiver complete a questionnaire using a secure online platform (https://sv.surveymonkey.com). Lab assessments take place at the first three assessment time points. Prior to each lab assessment, the child’s caregivers (legal guardians—when applicable) receive written information about the study purpose and procedures. Before each study visit, we collect written consent from the child’s caregivers. All participants are informed that that they have been given an anonymous identity number and that their data will be treated confidentially, that published reports of results from the study will be reported at a group level (meaning that it will not be possible to identify individuals), and that they can stop participating in the study at any time without giving any reasons. Participants are also informed that they have the right to have their data removed from the database at any time. During each study visit, the participating child’s caregiver is with the child at all time and can pause or stop data collection at any time. Similarly, the data collector pauses or stops the data collection during study visits if the child participant shows signs of discomfort or tiredness. Lab assessments last for up to 1.5 h, including breaks. The participants receive a gift card (€10) at each lab visit as a form of travel reimbursement.

### Criteria for discontinuing or modifying allocated interventions

Intervention session will be discontinued if participants request to withdraw from the study.

### Provision for post-trial care

Participants were informed about the risk associated with participating in the trial. Referrals were made if deemed appropriate and necessary. There were no plans for post-trial care.

#### Retention

Structures are in place to maximize participant retention. This includes making efforts to accommodate the participating caregiver and child when it comes to scheduling and re-scheduling of assessments, sending e-mail and text message reminders about upcoming scheduled assessment, group sessions and questionnaires, and sending information letters with updates on study progress to participating families.

### Data management

All data, including eye tracking data, EEG data, questionnaire data, and video records of observational task are submitted to a secure university server. All data are stored and managed according to current regulation on personal data management. Participants’ consent forms are stored in a locked storage area that is separate from the data obtained. All research data are “coded” and identified only by participant identification numbers to protect the participants identity and maintain confidentiality.

### Statistical methods

All statistical analysis will be conducted using the SPSS and R software. Data will be screened to check for data entry errors and to test if the data meet the assumptions of parametric procedures. The pattern and amount of missing data will be examined and handled by using maximum-likelihood estimates (or similar estimates), if appropriate. Baseline data and demographic characteristics will be described using summary statistics (means and standard deviations or number and percentages). Group baseline differences will be assessed using independent samples *t* test, chi-squared test, and Mann-Whitney *U* test. Fidelity in terms of adherence and the dose of the intervention will be summarized using descriptive statistics. All tests will be two-sided and 5% will be used as the level of significance. Effect size measures (e.g., Cohen’s *d*) will be calculated to describe intervention effects.

The statistical analyses of the primary outcomes will be performed blinded to treatment allocation. In accordance with CONSORT guidelines, intention-to-treat principles will be used to prevent systematic bias. Linear mixed models or analysis of covariance will be used to assess intervention effects at post intervention and at the follow-ups. Baseline scores will we controlled for as covariates. Other potential covariates (e.g., child monolingual status) will be investigated by examining correlations between covariates and the outcome variables.

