**Methods:**

We have conducted a randomized controlled trial to evaluate the effects of a parent-child interactive book sharing intervention on early child language, cognition, and parental behaviors. Participating caregivers and their 10-month-old child were randomized to an interactive book sharing intervention group (*n* = 59) or to an active control group (*n* = 56). The intervention was delivered by a facilitator to small groups of parent-child dyads on a weekly basis over 5 weeks. The primary outcomes were child language and socio-cognition; secondary outcomes were child executive function and parental scaffolding, sensitivity and reciprocity during book sharing, and problem-solving tasks. Data were collected at baseline, post-intervention, and at 6 and 12 months post-intervention.

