### Sample size

The originally targeted sample size was 140 children (10-month-old ± 4 weeks) and their caregivers (70 dyads in each arm). The sample size was calculated on the basis of the primary outcome measure language. The power calculation was conducted in G*Power [55] using 80% power and alpha set to = .05. The effect size (*d*) for the power calculation was based on the results reported in a recent meta-analysis by Dowdall et al. [26]. The meta-analysis [26] was based on RCT book sharing interventions targeting young children (1 to 6 years) and reported an overall effect size of *d* = .54 for expressive language in studies using medium to high intensity intervention dose (i.e., more than 60 min contact time). Based on this estimate, an index and control sample of 55 dyads in each arm would therefore be sufficient to detect a difference (two-tailed) and would allow for an attrition rate > 10%. The study’s final sample size was 115 parent-child dyads (index group, *n* = 59; active control group, *n* = 56). Thus, the study’s sample size is sufficiently powered.

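### The abstract gives 115 dyads as randomised where Recruitment gives 151, and the unqualified intention-to-treat claim does not fit the 36 (23.8%) lost before baseline

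*Protocol article*

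**What the plan says.** The Recruitment section gives the participant flow. "Of 187 dyads assessed for eligibility, 151 met all inclusion criteria and none of the exclusion criteria and gave consent to participate in the study". It continues: "They were then randomized to an index group or active control group". Then: "Of these, 115 completed the baseline assessment, 109 completed the post-assessment, and 98 completed the first follow-up assessment at 18 months". Read in order, that is 151 randomised, then 115, 109 and 98 assessed.

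The abstract gives a different count. "Participating caregivers and their 10-month-old child were randomized to an interactive book sharing intervention group" with n = 59, or to the active control group with n = 56, which makes 115.

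The Sample size section states that the "final sample size was 115 parent-child dyads" (59 and 56) and judges power adequate on that number.

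On timing, the Concealment mechanism section says allocation was released to participants after recruitment and after "giving consent to being part of the study prior to baseline assessment". The Blinding section adds that participants are not blinded and know that there is a reading group and a play group.

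The Statistical methods section makes the analysis commitment: "In accordance with CONSORT guidelines, intention-to-treat principles will be used to prevent systematic bias". It plans linear mixed models or analysis of covariance with baseline scores as covariates, and maximum-likelihood handling of missing data where appropriate.

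**The concern.** The abstract and the Recruitment section cannot both be right about how many dyads were randomised. Recruitment sets out the full flow, so 59 and 56 are best read as the dyads who completed baseline.

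The number matters because intention-to-treat is defined by who was randomised. If about a quarter of the randomised dyads leave before any measurement, the two groups that remain no longer have the full protection of randomisation. The plan nevertheless offers intention-to-treat, without qualification, as its guard against systematic bias. A reader who takes 115 as the denominator will also judge attrition to be much lower than it is.

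**Working it through.** **The plan's own sample-size figure.** Inputs from the Sample size section are d = 0.54, 80% power and two-sided alpha 0.05. The normal approximation gives n = 2(1.960 + 0.842)²/0.54² = 53.8, so 54 per arm. The noncentral t calculation gives 54.81, so 55 per arm. The stated 55 reproduces and is not at issue.

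**The denominator.** Inputs are 151, 115, 109 and 98, all from Recruitment.

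| Stage | Assessed | Lost, from 151 | Lost, from 115 |
|---|---|---|---|
| Baseline | 115 | 36 (23.8%) | – |
| Post-assessment | 109 | 42 (27.8%) | 6 (5.2%) |
| 18 months | 98 | 53 (35.1%) | 17 (14.8%) |

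**Whether the planned analysis can include the 36.**
- They did not complete baseline, so on the natural reading they lack the covariate that the models require.
- Recruitment does not count them as completing any later assessment, and the final sample is given as 115.
- A dyad with neither a baseline nor an outcome value tells a maximum-likelihood analysis nothing about how its outcome departs from the others in its arm.

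The analysis would therefore in effect cover at most the 115.

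**How large a bias could be (illustration only).** The arm split of the 151 is not given. Assume 75 index and 76 control. Losses before baseline are then 75 − 59 = 16 (21.3%) and 76 − 56 = 20 (26.3%). Assume also that leavers differ by 0.5 SD from stayers in their own arm. The shift in an arm's mean is 0.5 × the proportion lost:
- index: 0.5 × 16/75 = 0.107 SD
- control: 0.5 × 20/76 = 0.132 SD

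The bias in the contrast between arms is then:
- same direction in both arms: 0.132 − 0.107, about 0.02 SD
- one arm only: 0.11 to 0.13 SD
- opposite directions: 0.107 + 0.132, about 0.24 SD

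If the 0.5 SD is instead measured from the mean of the whole randomised arm, the shift is 0.5 × lost/stayed. That is 0.5 × 16/59 = 0.136 and 0.5 × 20/56 = 0.179, so about 0.04, 0.14 to 0.18, and 0.31 SD. The planning effect is 0.54 SD. None of these scenarios is a finding about this trial.

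**The case against.** **The plan does not say that it excludes the 36.** This is correct. Statistical methods names no analysis set, and an article may leave that to the statistical analysis plan. The exclusion is inferred from the final sample of 115, the baseline-adjusted models and the absence of any later count for these dyads. A separate analysis plan could define the set, but it could not reconcile two different numbers randomised in the published article.

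**The flow is disclosed.** This is also correct: a careful reader of Recruitment has the right denominator. The Sample size section calls 115 the final sample, not the number randomised, so only the abstract misstates that number.

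**Families may not have known their arm when they left.** The sentence on releasing allocation is awkward, and its reference to baseline could attach to the giving of consent. The plain reading is disclosure before baseline, and Recruitment independently places randomisation before baseline. Still, nothing shows that all 36 had been told before they dropped out.

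**The losses may have nothing to do with arm.** A reader might infer that a bias has already occurred. The documents do not support that, because they give no reasons for loss and no split by arm. An arm-neutral route is conceivable: Trial status reports recruitment pauses during the COVID-19 pandemic, and eligibility requires a child aged 10 months ± 4 weeks at baseline, so some children may have passed the age limit. The documents do not link the pauses to these losses either. The same mechanism in both arms would leave little bias, as the illustration shows, and baseline adjustment might absorb part of any imbalance.

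**Conclusion.** The point holds in a limited form. The abstract's number randomised contradicts the Recruitment section. The unqualified intention-to-treat claim does not fit a trial in which 36 of 151 randomised dyads (23.8%) apparently have no baseline or later data. What the plan can deliver is an as-randomised comparison of the dyads who completed baseline.

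This rests on two readings: that Recruitment is the authoritative flow, and that the 36 supplied no usable data. That the losses could depend on arm rests further on disclosure before baseline. Neither the existence nor the direction of a bias can be established, and the SD figures above are illustrative. The attrition percentages need no assumption beyond the denominator.

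**What to change.** 1. In the abstract, state that 151 dyads were randomised, by arm, and describe 59 and 56 as the dyads completing baseline.
2. Report the 36 losses between randomisation and baseline by arm and by reason, and say whether the family had been told its arm.
3. Replace the unqualified claim with *modified intention-to-treat: randomised dyads who completed baseline, analysed as randomised regardless of attendance*.
4. Report attrition at each assessment from 151. The figure from 115 can stand beside it.
5. Optionally, add a sensitivity analysis with arm-specific shifts for dyads without post-assessment data. For the 36 without baseline its result would be largely assumption, so it supplements the first four steps and does not replace them.

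The first four steps need only wording and records that the trial should already hold, with no new participant data. The price is a less favourable flow diagram and a weaker claim about protection from bias.
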